# Feasibility of electroacupuncture at Baihui (GV20) and Zusanli (ST36) on survival with a favorable neurological outcome in patients with postcardiac arrest syndrome after in-hospital cardiac arrest: study protocol for a pilot randomized controlled trial

**DOI:** 10.1186/s40814-023-01239-9

**Published:** 2023-01-13

**Keywords:** Cardiac arrest, Postcardiac arrest syndrome, Cardiopulmonary resuscitation protocol, Electroacupuncture

## Abstract

**Background:**

At present, even the first-line medication epinephrine still shows no evidence of a favourable neurological outcome in patients with sudden cardiac arrest (SCA). The high mortality of patients with postcardiac arrest syndrome (PCAS) can be attributed to brain injury, myocardial dysfunction, systemic ischaemia/reperfusion response, and persistent precipitating pathology. Targeted temperature management, the only clinically proven method in the treatment of PCAS, is still associated with a series of problems that have not been completely resolved.

Acupuncture is a crucial therapy in traditional Chinese medicine. On the basis of the results of previous studies, we hypothesize that electroacupuncture (EA) might provide therapeutic benefits in the treatment of PCAS. This study will explore the feasibility of EA on SCA patients.

**Methods:**

This is a prospective pilot, randomized controlled clinical trial. Eligible patients with PCAS after in-hospital cardiac arrest (IHCA) admitted to our department will be randomly allocated to the control group or the EA group. Both groups will receive standard therapy according to American Heart Association guidelines for cardiopulmonary resuscitation. However, the EA group will also receive acupuncture at the Baihui acupoint (GV20) and Zusanli acupoint (ST36) with EA stimulation for 30 min using a dense-dispersed wave at frequencies of 20 and 100 Hz, a current intensity of less than 10 mA, and a pulse width of 0.5 ms. EA treatment will be administered for up to 14 days (until either discharge or death). The primary endpoint is survival with a favourable neurological outcome. The secondary endpoints are neurological scores, cardiac function parameters, and other clinical parameters, including Sequential Organ Failure Assessment (SOFA) scores and Acute Physiology and Chronic Health Evaluation (APACHE) II scores, on days 0 to 28.

**Discussion:**

This study will provide crucial clinical evidence on the efficacy of EA in PCAS when used as an adjunctive treatment with AHA standard therapy.

**Trial registration:**

chictr.org.cn: ChiCTR2000040040. Registered on 19 November 2020. Retrospectively registered. http://www.chictr.org.cn/.

**Supplementary Information:**

The online version contains supplementary material available at 10.1186/s40814-023-01239-9.

## Background

Sudden cardiac arrest (SCA) is a significant cause of death worldwide, and more than 550,000 deaths due to SCA occur annually in the USA and Europe [1]. A recent study showed that epinephrine, the first-line medication for patients with SCA, was associated with more severe neurological impairment in survivors than placebo in adults with out-of-hospital cardiac arrest (OHCA) [2]. In addition, SCA patients will have sepsis-like changes, which may be caused by ischaemia, hypoxia, and reperfusion injury, after the return of spontaneous circulation (ROSC), resulting in multiple organ dysfunction syndromes (MODSs) and a poor prognosis,. This series of reactions is called postcardiac arrest syndrome (PCAS) [3]. According to studies performed in the USA, Europe, and Asia, whether in adults, children, or infants, the mortality rate of PCAS patients is 65–80% [4–8]. The high mortality rate can be attributed to a unique pathophysiological process. The special features of this unique pathophysiological process of PCAS are often superimposed on the disease or injury that caused the cardiac arrest and underlying comorbidities [3]. There are four critical components of PCAS: brain injury [9, 10], myocardial dysfunction [11, 12], systemic ischaemia/reperfusion response [13], and persistent precipitating pathology [14]. Therefore, therapies focusing on a single organ may further damage other damaged organ systems. Targeted temperature management (TTM) is currently the only clinically proven method to improve SCA patients’ survival and neurological outcomes after the ROSC [15, 16]; however, TTM is still associated with a series of problems that have not been completely resolved [17].

Acupuncture is a crucial therapy in traditional Chinese medicine (TCM). Acupuncture involves the insertion of fine needles at “acupoints”, followed by stimulation via manual or mechanical techniques [18]. It has been reported that acupuncture may have a bidirectional regulating effect and an anti-systemic inflammatory response effect [19, 20]. The acupuncture effect of balancing the autonomic nervous system has been demonstrated to inhibit neuronal apoptosis and reduce oxidative stress [21–23]. These effects are in line with the critical components of PCAS mentioned above.

Nevertheless, the effects of acupuncture on PCAS have never been investigated comprehensively. Therefore, the present pilot, randomized, controlled study was designed to explore the feasibility of electroacupuncture (EA) on PCAS patients and furthermore evaluate the impact in the main trial.

The specific objectives of this pilot study were to test the trial procedures, explore the feasibility of the program, and provide data for recruitment, follow-up rates, and sample size calculation for the main trial.

## Method

### Aim

The study is a prospective randomized controlled pilot trial designed to evaluate whether EA can improve survival with a favorable neurological outcome of PCAS after in-hospital cardiac arrest (IHCA).

### Design

This study is a prospective randomized controlled pilot clinical trial that will be carried out in the Emergency Department of Guangdong Provincial Hospital of Chinese Medicine and Intensive Care Unit of Fangcun Branch Hospital of Guangdong Provincial Hospital of Chinese Medicine. This trial is embedded with a study of survival with a favourable neurological outcome of PCAS following IHCA.

The trial received ethics approval from the Guangdong Provincial Hospital of Chinese Medicine Institutional Review Board (approval number ZF2020-051-01). If any changes are made to this protocol, a draft of the new version must be submitted for approval by the Institutional Review Board of Guangdong Provincial Hospital of Chinese Medicine. This clinical trial will conform to the national laws and the principles of the Declaration of Helsinki. The eligible participants’ authorized representatives will sign informed consent papers before the participants are enrolled.

The protocol adheres to the Standard Protocol Items: Recommendations for Interventional Trials (SPIRIT) guidelines (Additional file 1).

### Participant selection criteria

Patients aged 18 to 85 years who suffer SCA in the hospital caused by respiratory failure or hypovolemic shock and with a ROSC sustained for ≥ 20 min and met the following criteria at the same time are eligible to enrol in this study: Glasgow coma score ≤ 8 after ROSC, and before sedation (if any); the legal representative signed the informed consent; advanced cardiovascular life support is conducted. Those who meet the exclusion criteria (listed in Table 1) will not be enrolled in this study.

**Table 1 Tab1:** Inclusion and exclusion criteria

A. Inclusion criteria for observational part	
1. Cardiac arrest is caused by respiratory failure or hypovolemic shock;	
2. In-hospital cardiac arrest;	
3. Aged 18–85 years old;	
4. Patients with return of spontaneous circulation (ROSC) that is sustained for ≥ 20 min;	
5. Glasgow coma score ≤ 8 after ROSC, and before sedation (if any) ;	
6. The legal representative signed the informed consent;	
7. Advanced cardiovascular life support is conducted.	
B. Exclusion criteria	
1. No-flow time > 10 min (time from collapse to initiation of external cardiac massage);	
2. Low-flow time > 60 min (time from initiation of external cardiac massage to ROSC);	
3. Major hemodynamic instability (defined as a continuous epinephrine or norepinephrine infusion at a flow rate > 1 μg/kg/min);	
4. Cardiac arrest caused by advanced tumor and other end-of-state diseases;	
5. Cardiac arrest caused by an irreversible cause (such as severe trauma and poisoning);	
6. Cardiogenic cardiac arrest (acute infarction, malignant arrhythmia, heart failure, etc.);	
7. Acupoint with lesions, wounds, or skin diseases affects acupuncture;	
8. Allergic persons, or known to be allergic to treatment, such as metal;	
9. Pregnant or lactating women.	

Participants can withdraw from the trial for any reason at any time. Participants for whom, upon regaining consciousness (if any), the legal representative or patient requests study withdrawal may be removed from the study:

The flow chart of the study is presented in Fig. 1.

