### Randomization

Eligible patients enrolled in this trial will be randomly assigned to the EA or control groups in a 1:1 ratio. Randomization assignment will be carried out by a researcher ([name]) not involved in the treatment and assessment. This randomization will be run with a block randomization size of four by SPSS 17.0. The randomization block size will be concealed to guarantee rigorous methodology, and the allocation number will be sequentially assigned and stored. The unique code assigned to each newly eligible participant will be adequately preserved throughout this study. This procedure will ensure that each eligible patient could be assigned to either of the two groups with equal probability and that group assignment will not be influenced by the researchers. [name] and [name] will enrol and assign participants to interventions according to the preprepared allocation sequence. Considering that an included patient could withdraw from the study, their randomization number would be invalidated, so we will ultimately take the first 52–60 patients. Finally, the number of patients in these two groups may be different because of the actual procedures performed.

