### EA treatment

Disposable stainless steel acupuncture needles will be inserted at the Baihui acupoint (GV20, located at the intersection of the sagittal midline and the line linking the ears) and unilaterally on the side of the left leg at the Zusanli acupoint (ST36, situated on the front to one side of the leg, 3 *cun* below the acupoint ST35 and a cross-finger (middle finger) away from the leading edge of the tibia) to a depth of approximately 0.5 cm [28]. Furthermore, an EA instrument (Suzhou Medical Supplies Factory Co., Ltd., Jiangsu, China) will be connected to perform EA stimulation for 30 min using a dense-dispersed wave at frequencies of 20 and 100 Hz. The current intensity will be less than 10 mA (adjusted to induce a slight muscle twitch), and the pulse width will be 0.5 ms. One of the two electrodes of the EA stimulator will be connected to the needle at GV20, and the other electrode will be connected to the needle at ST36. This EA intervention will begin immediately after the ROSC for 20 min and will continue for up to 14 days, discharge, or death, whichever comes first. The EA will be performed by [name], [name], or [name], who will conduct the research and have previously received equal training.

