### Outcome measures

The primary feasibility outcomes are as follows:Evaluate the acceptability and compliance of EA in PCAS as an additional intervention of usual care.Explore the feasibility of recruiting, randomizing, and retaining participants.Evaluate outcome measures’ appropriateness.Collect data for effect size calculation in future sample size calculating.Develop an appropriate protocol for further study.

The length of time for recruitment of 50 eligible patients, recruitment rate and dropout rate will be measured. Successful recruitment is defined as at least half (50%) of eligible patients enrolled, with a dropout rate of no more than 20%.

The secondary patient-centred outcomes include the following:We define a favourable neurological outcome as a cerebral performance category (CPC) score of 1 or 2 on the 28th day after the ROSC. We define an ROSC as a spontaneous pulse and blood pressure, an abrupt sustained increase in end-tidal CO_2_ partial pressure (PETCO_2_) (typically ≥ 40 mmHg), or spontaneous arterial pressure waves with intra-arterial monitoring.Neurological scores: Glasgow Coma Scale (GCS) score, CPC score, modified Rankin Scale (mRS) score, and cranial computed tomography (CT) findings;Evaluation of cardiac function: troponin and lactic acid levels and echocardiography parameters.Sequential Organ Failure Assessment (SOFA) scoresAcute Physiology and Chronic Health Evaluation (APACHE) II scoresLength of stay in the ICU, length of hospital stay, hospital mortality/discharge, and hospital costsAdverse events

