### Statistical analysis

The data will be analysed statistically according to the method of a previous study [32]. Enrolled participants who cannot continue the study or follow up after treatment will remain in an “intention to treat” analysis. All statistical analyses will be performed with SPSS (version 17.0, Chicago, USA) for Windows by researchers not implementing the intervention. The analysis of this trial will be mainly descriptive focusing on estimation rather than hypothesis testing. All baseline outcomes will be summarized for each group using the appropriate descriptive statistics. No formal comparison of groups will take place. A full statistical analysis plan will be developed prior to the final analysis of the trial.

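### Removing patients who withdraw on waking and voiding their randomisation numbers conflicts with the intention-to-treat statement and, if followed, would lower the observed favourable-outcome rate

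*Protocol article*

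**What the plan says.** Three sections of the protocol article deal with patients who leave the trial.

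- **Participant selection criteria** (text under Table 1) first gives a general right: "Participants can withdraw from the trial for any reason at any time". It then adds a clause for one situation: "Participants for whom, upon regaining consciousness (if any), the legal representative or patient requests study withdrawal may be removed from the study". It does not say whether removal ends EA, ends follow-up, or discards data already collected.
- **Randomization** says of a patient who withdraws that "their randomization number would be invalidated, so we will ultimately take the first 52–60 patients". It goes on to accept that the two groups may end up unequal in size.
- **Statistical analysis** says: "Enrolled participants who cannot continue the study or follow up after treatment will remain in an “intention to treat” analysis".

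The clinical outcome concerned is a "cerebral performance category (CPC) score of 1 or 2 on the 28th day after the ROSC" (Outcome measures). The Abstract calls survival with a favourable neurological outcome the primary endpoint; Outcome measures lists it among the secondary patient-centred outcomes. All patients enter with a Glasgow score of 8 or less, on a representative's consent.

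**The concern.** Because consent at entry comes from a representative, waking is the first moment at which patients can decide for themselves, so requests to leave at that point are foreseeable. Waking is also a necessary step towards CPC 1 or 2. If a patient who asks to leave then is taken out of the analysis, the chance of being taken out depends on the outcome being measured. A patient who never wakes can leave only under the general right.

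The pilot exists to supply follow-up rates and sample-size inputs for the main trial (end of Background) and data for an effect-size calculation (Outcome measures). A favourable-outcome rate computed without some of its successes would pass into that planning. The same withdrawals count against the feasibility criterion of no more than 20% dropout, so recovery itself could make retention look worse.

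**Working it through.** **1. The planned number.** Sample size determination starts from 20 or more participants and expects 20% dropout. Reading 20 as per arm, 2 × 20 / (1 − 0.20) = 40 / 0.80 = 50, which reproduces the plan's 50. Reading 20 as the total gives 20 / 0.80 = 25, which does not. The 52–60 in Randomization exceeds 50 and is explained there by withdrawn patients' numbers being invalidated. That supports reading the section as replacement.

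**2. The sections side by side.**

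| Section | What happens to a patient who leaves |
|---|---|
| Participant selection criteria | May be removed from the study if withdrawal is requested on waking |
| Randomization | Number invalidated; the first 52–60 patients are taken |
| Statistical analysis | Stays in an intention-to-treat analysis |

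The second and third rows cannot both govern the analysis set. The first does not say which of them it follows.

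**3. Effect on the rate if removed patients are not analysed.** Let p be the true proportion with CPC 1 or 2, and w the share of those patients who are removed, everyone else being kept. The observed proportion is

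p(1 − w) / (1 − pw).

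The protocol gives neither p nor w, so both are assumed. Its Background cites 65–80% mortality in post-cardiac-arrest syndrome, which implies 20–35% survival, a ceiling on p if this population is similar.

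| p | w | Calculation | Observed | Expected removals among 25 |
|---|---|---|---|---|
| 0.20 | 0.1 | 0.18 / 0.98 | 18.4% | 0.5 |
| 0.20 | 0.2 | 0.16 / 0.96 | 16.7% | 1.0 |
| 0.20 | 0.4 | 0.12 / 0.92 | 13.0% | 2.0 |
| 0.30 | 0.2 | 0.24 / 0.94 | 25.5% | 1.5 |
| 0.30 | 0.4 | 0.18 / 0.88 | 20.5% | 3.0 |

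One to three patients per arm of 25 are enough to move the rate by about 3 to 10 percentage points.

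**4. Effect on the comparison between arms.**

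- *Same p, same w:* both arms fall equally and the difference stays at zero.
- *Assumed benefit (20% control, 35% EA), w = 0.2 in both:* observed 16.7% and 0.28 / 0.93 = 30.1%. The risk difference goes from 15.0 to 13.4 points, the risk ratio from 1.75 to 1.81, and the odds ratio stays at 2.15. EA loses more in absolute terms (4.9 against 3.3 points) but keeps a larger share of its rate (0.86 against 0.83).
- *No true effect (20% in both), w = 0.3 in EA and 0.1 in control:* 0.14 / 0.94 = 14.9% against 18.4%, a false deficit of 3.5 points for EA.

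**5. If every patient is kept with a known day-28 CPC,** the rate stays at p and nothing is lost.

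**The case against.** A patient who regains capacity must be free to leave; that right is no flaw. A reader might infer that waking itself triggers removal, so that only future CPC 1 or 2 patients can be lost. The text does not support this. The trigger is a request, removal is optional, the general right covers everyone in either arm, and waking is not the same as CPC 1 or 2 at day 28. The sentence also ends in a colon with nothing after it, so qualifying text may be absent from the article.

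A reader might also infer that the outcome is certainly depleted. That follows only if the removal and invalidation wording overrides the intention-to-treat statement, which the protocol leaves open.

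The most tempting inference is that the bias falls mainly on EA. There is a reason to suspect it: EA "will continue for up to 14 days, discharge, or death, whichever comes first", and the Discussion acknowledges that participants are not blinded. But controls have continuing study contact too. Data acquisition schedules findings for all participants up to day 28 and recalls those discharged early. An example that starts from 5 of 25 in each arm and removes two favourable patients from EA alone gives 3/23 = 13.0% against 20%. The arithmetic is right, but the one-sidedness is put in by hand.

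Finally, the analysis is descriptive, no formal comparison is planned, and bounds or by-arm withdrawal tables could be left to the promised analysis plan. This lowers the stakes for inference. It does not remove the conflict between sections, and no analysis plan can restore a day-28 CPC that was never collected.

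**Conclusion.** The point holds as a conflict within the protocol with a foreseeable outcome-related consequence. Removal and invalidation cannot stand beside an intention-to-treat analysis. If they are what is done, withdrawals at waking lower the observed favourable-outcome rate: from an assumed 20% to between 18.4% and 13.0% when 10% to 40% of favourable patients are removed. These rates and shares are assumptions; the protocol gives no CPC 1 or 2 rate and no withdrawal rate at waking.

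An imbalance between arms is possible but not documented. It needs unequal withdrawal or a true difference in outcome, and with equal withdrawal and no true effect the difference stays at zero. The matter deserves correction now because recruitment is under way and follow-up not obtained may be unrecoverable.

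**What to change.** Reconcile Participant selection criteria and Randomization with Statistical analysis.

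- Replace removal from the study by a statement that a patient or representative may stop EA, study contact, or both at any time, and treat withdrawal of data as a separate, explicit request.
- State that data collected to that date are kept, and that day-28 CPC and vital status are taken from routine records unless this is specifically refused.
- State that randomisation numbers are neither voided nor replaced, and align the 52–60 with the planned 50.
- Report withdrawals by arm and by whether the patient had regained consciousness.
- Give the favourable-outcome proportion for all randomised patients, with bounds counting those with missing day-28 CPC first as unfavourable and then as favourable. For example, in an arm of 25 with five true successes of whom two are lost, the bounds are 3/25 = 12% and 5/25 = 20%, in place of a single 3/23 = 13.0%.

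The cost is a minor amendment to the protocol and consent form, and slightly wider reported ranges. No extra patients or visits are needed.

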**Fig. 1 Fig1:**
[figure not shown]
Study flow chart. CA, cardiac arrest; ROSC, return of spontaneous circulation; BLS, basic life support; CPR, cardiopulmonary resuscitation; ACLS, advanced cardiovascular life support; ICU, intensive care unit; EA, electroacupuncture; CPC, cerebral performance category; GCS, Glasgow Coma Scale; CT, computed tomography; SOFA, Sequential Organ Failure Assessment; APACHE, Acute Physiology and Chronic Health Evaluation

### Randomization

Eligible patients enrolled in this trial will be randomly assigned to the EA or control groups in a 1:1 ratio. Randomization assignment will be carried out by a researcher ([name]) not involved in the treatment and assessment. This randomization will be run with a block randomization size of four by SPSS 17.0. The randomization block size will be concealed to guarantee rigorous methodology, and the allocation number will be sequentially assigned and stored. The unique code assigned to each newly eligible participant will be adequately preserved throughout this study. This procedure will ensure that each eligible patient could be assigned to either of the two groups with equal probability and that group assignment will not be influenced by the researchers. [name] and [name] will enrol and assign participants to interventions according to the preprepared allocation sequence. Considering that an included patient could withdraw from the study, their randomization number would be invalidated, so we will ultimately take the first 52–60 patients. Finally, the number of patients in these two groups may be different because of the actual procedures performed.

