### Blinding and masking

Since this study involves acupuncture, it is challenging to achieve double blindness. However, to avoid bias in this process, the following specific measures are proposed:Participants will be recruited in strict accordance with the principle of randomization.The physicians participating in the outcome evaluation will be nonresearchers, making the trial efficacy evaluation blinded.The laboratory technicians and the biostatisticians will be blinded to the assigned treatments.

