### Trial status

We are currently recruiting participants.

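### The Randomization section promises concealed, uninfluenced allocation, but it prints one fixed block size of four during open recruitment and has the same two people enrol and assign.

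*Protocol article*

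**What the plan says.** All the allocation rules stand in the Randomization section of the protocol article.

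- Patients are "randomly assigned to the EA or control groups in a 1:1 ratio".
- Assignment is first given to a researcher "not involved in the treatment and assessment". Independence from enrolment is not mentioned.
- The method is one fixed block size: "This randomization will be run with a block randomization size of four by SPSS 17.0". No stratification is described.
- The next sentence promises: "The randomization block size will be concealed to guarantee rigorous methodology".
- The section then assures the reader that "group assignment will not be influenced by the researchers".
- Straight after that assurance, two named people "will enrol and assign participants to interventions according to the preprepared allocation sequence".

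Three other places bear on this. Trial status says "We are currently recruiting participants", in an article dated 13 January 2023. Blinding and masking concedes that "it is challenging to achieve double blindness" and limits blinding to outcome evaluators, laboratory technicians and biostatisticians. The Discussion lists the lack of participant blinding as a limitation.

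**The concern.** Concealment needs two things: whoever decides that a patient enters must not know the next assignment, and must not be able to work it out. The section weakens both. It puts enrolling and assigning in the same hands, and it publishes the one parameter it says is hidden. Treatment is visible to staff, since needles and a stimulator are used for up to 14 days in one arm only, so earlier assignments can be known.

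Entry leaves room for judgement. Someone must attribute the arrest to respiratory failure or hypovolemic shock, rule out an irreversible cause, score the coma scale before sedation and approach a legal representative. An enroller who expects a particular arm may, without intending to, approach, judge or present consent differently.

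This matters in a pilot too. Outcome measures defines successful recruitment as at least half of eligible patients enrolled, and lists effect-size data for the main trial among the feasibility aims. Selective entry would distort both, and analysis cannot reliably remove it. The Background says the pilot is to test the trial procedures, so a weak allocation procedure would also carry forward.

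**Working it through.** **Inputs.** Ratio 1:1 and block size 4 (Randomization). Planned N is 50 (Sample size determination; Outcome measures) but 52 to 60 in Randomization. Alpha, power and effect size play no part.

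**The plan's own figure.** Reading the recommended 20 as per arm, 40 / (1 − 0.20) = 50, so the planned N reproduces (20 in total would give 25). Fifty is 12 complete blocks of four plus 2 patients.

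**Predictability of one block.** There are six equally likely orderings: AABB, ABAB, ABBA, BAAB, BABA, BBAA. Assume the observer knows the block size and all earlier assignments in the block, guesses the arm that lags, and tosses a coin when the arms are level.

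| Position | Probability assignment is already fixed | Probability of a correct guess |
|---|---|---|
| 1 | 0 | 1/2 |
| 2 | 0 | 2/3 |
| 3 | 1/3 | (1/3)(1) + (2/3)(1/2) = 2/3 |
| 4 | 1 | 1 |
| Sum | 4/3 | 17/6 |

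Share known for certain: (4/3)/4 = 1/3, or 8 of 24 positions. Share guessed correctly: (17/6)/4 = 17/24 = 70.8%, against 50% by chance.

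**Whole-trial ceilings**, if that knowledge held from the first patient to the last:

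- N = 50: certain 12 × 4/3 = 16.0; guessed 12 × 17/6 + 1/2 + 2/3 = 35.2 (70.3%).
- N = 52: certain 13 × 4/3 = 17.3; guessed 13 × 17/6 = 36.8 (70.8%).
- N = 60: certain 15 × 4/3 = 20.0; guessed 15 × 17/6 = 42.5 (70.8%).

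If enrollers learned the block size only from publication, the number certain is about one third of the patients still to come. That number is not given, so the range runs from 0 to the ceilings above.

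**What varied blocks would do** (simulation at N = 50, 20,000 runs, observer tracking only the running imbalance):

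| Block sizes | Certain | Guessed correctly |
|---|---|---|
| Fixed 4 | 8.0% | 70.3% |
| Random 2/4/6 | 0.8% | 70.0% |
| Random 4/6/8 | 0.2% | 67.7% |

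This observer does not use the position within the block, so the like-for-like figure for fixed fours is 8.0%; it is 16/50 = 32% when position is used. Someone who knew the set of sizes could sometimes deduce more: with 2/4/6, an opening AABA can only belong to a block of six, so BB must follow. That is a reason to leave the sizes unpublished. Certain knowledge falls sharply, while guessing hardly moves.

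**The case against.** The strongest reply is that the text has a benign reading. The sentence about the independent researcher is followed at once by the software and block size, so it may describe generating the list, and the later sentence its implementation. With names removed from the text reviewed, one of the two people may enrol and the other assign. The section also says allocation numbers are given in sequence and stored, and a condensed article may leave the release device to the full protocol. All of that is fair, and the absence of an envelope or telephone procedure is not the point here. What stands is what the article does state: a hidden block size that it prints, and enrolling and assigning given jointly to the same pair. No release device described elsewhere makes those sentences consistent.

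A reader might infer three stronger things that the documents do not support.

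- That enrollers hold the open list, so every assignment is known. Nothing says so.
- That about 16 or 17 assignments are certain in advance. The trial was registered retrospectively on 19 November 2020, so recruitment may have run for over two years before publication. Recruitment also covers two units (Design): if one list serves both, an enroller must also know the other unit's assignments.
- That a promising patient could be held back for an EA slot. EA treatment starts the intervention once circulation has been sustained for 20 minutes after an unscheduled arrest, which leaves little room for deferral. Selective approach, judgement or consent is the plausible route.

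The pilot's status also counts. Statistical analysis plans description without formal group comparison, and the Discussion calls the clinical results preliminary. That lowers the severity, but the recruitment rate and effect-size data remain exposed.

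**Conclusion.** The point holds as an internal contradiction with a bounded consequence. The section does not deliver the concealment it claims, and its assurance about researcher influence is unsupported as written. The size is at most one third of assignments certain and about 71% guessable. Both figures assume that the enroller knows the block size and every earlier assignment in the block, at both units if they share one list. They are ceilings, not estimates, and the documents give no evidence that allocation has been subverted. Given the descriptive analysis, this should be fixed for the patients still to be recruited; it is not a fatal flaw.

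**What to change.** For the remaining patients:

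1. Rewrite the Randomization section so that the sentences on who assigns agree. The independent researcher alone holds the sequence, and those who enrol do not.
2. Release each assignment only after eligibility, consent and baseline data are irrevocably logged. Use the ResMan platform already in use if it supports this, otherwise telephone or sequentially numbered opaque sealed envelopes.
3. Generate the remaining sequence with randomly varied block sizes and do not publish them until recruitment closes. Remove or correct the statement that the present block size is concealed.

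Steps 1 and 2 are essential. Step 3 removes nearly all certain knowledge but leaves guessing at about 70% (2/4/6) or 68% (4/6/8). When the change is made, state one planned N, since 50 and 52 to 60 both appear.

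The cost is a small release procedure, which must work whenever an arrest occurs, and a new list from the researcher already designated. The new sequence could end up to 3 patients out of balance with blocks up to 6, or 4 with blocks up to 8, against 2 with fixed fours.
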